## Abstract

**Background:**

Lumbar disc herniation (LDH) has become a serious public health and socioeconomic problem. Tuina is a Chinese medicine treatment method based on meridian acupuncture theory and modern anatomy. Tuina can relieve pain and muscle tension and improve functional disorders; this massage is performed by pressing, kneading, pushing, pulling, and shaking the skin, muscles, and bones. However, the mechanism of action and the effect of Tuina as an external treatment on the activities of the central nervous system to relieve LDH pain is unclear. Therefore, we performed functional magnetic resonance imaging (fMRI), which is widely used in pain-related research, as it can detect the effects of different types of pain on brain activity.

**Objective:**

Our randomized controlled parallel-group trial aims to compare the effects of Tuina with those of transcutaneous electrical nerve stimulation (TENS) with traction in patients with LDH.

**Methods:**

This trial will be conducted between May 2024 and April 2025 in the Rehabilitation Hospital affiliated to Fujian University of Traditional Chinese Medicine. Seventy-six participants with LDH will be enrolled for this trial and randomly assigned to 2 groups: Tuina intervention group and TENS with traction intervention group. Participants in both groups will receive treatment for 14 days. fMRI will be performed for the main pain measurements by assessing the effect of the intervention on brain activity before and after the end of the intervention. Short-Form McGill Pain Questionnaire, pressure pain thresholds, and the Oswestry disability index will be used to reflect the degree of pain and lumbar dysfunction, and the results will be used as secondary outcome measurements.

**Results:**

The study protocol has been approved by the ethics review committee of The Rehabilitation Hospital affiliated to Fujian University of Traditional Chinese Medicine. This study was registered on May 1, 2024, with the Chinese Clinical Trial Registry. Data collection began on May 2024 and is expected to end on April 2025. Currently, data from this trial are in the collection phase, and no data analysis has been performed. As of July 1, 2024, we have collected data from 21 patients. The results of this trial are expected to be submitted for publication in September 2025.

**Conclusions:**

This clinical trial will compare the effectiveness of Tuina with that of TENS with traction in the treatment of patients with LDH and will show the cerebral mechanism of Tuina in LDH treatment by using fMRI. The results of our trial will be helpful in clarifying the cerebral mechanism of Tuina in the treatment of LDH and provide a solid foundation for Tuina therapy research.

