## Methods

### Trial Design

This is a single-center randomized controlled trial with 2 parallel arms: the Tuina intervention group and traction with transcutaneous electrical nerve stimulation (TENS) intervention group. A total of 76 eligible patients with LDH will be recruited for this trial, and patients with LDH will be randomly assigned to the groups in 1:1 ratio. All patients will provide written informed consent. Outcome evaluation and statistical analysis will be performed by 2 researchers who do not know the specific groups. The trial design flowchart is shown in Figure 1, and the study schedule is shown in Figure 2. This study will be conducted in the Rehabilitation Hospital affiliated to Fujian University of Traditional Chinese Medicine. This study follows the CONSORT (Consolidated Standards of Reporting Trials) guidelines (Multimedia Appendix 1).

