### Inclusion Criteria

The inclusion criteria for the participants are as follows: (1) right-handed; (2) age between 18 and 60 years; (3) computed tomography or magnetic resonance imaging examination show L4-L5 or L5-S1 disc herniation; (4) the main manifestation is nerve root pain, and the imaging is consistent with the nerve localization; (5) the neuropathic pain rating scale (Douleur Neuropathique 4 questions) score is ≥4; (6) patients who did not take painkillers or nutritional neurodrugs for nearly 1 month and did not receive systematic treatment; and (7) patients who voluntarily want to participate in clinical trials and sign informed consent forms.

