### Statistical Analysis

Statistical analysis will be conducted using SPSS 26.0 statistical software. Count data will involve the ratio of the sex and age variables compared between the 2 groups via the *χ*^2^ test of the 4-fold table or the Fisher test. The SF-MPQ scores, PPTs, and ODI scores are the rank data. Therefore, the Mann-Whitney *U* test will be used for the intergroup comparison, and the Wilcoxon symbolic test will be applied for the intragroup comparison. Paired 2-sided *t* test will be used to assess the difference in ALFF and ReHo between the 2 groups. In addition, Pearson correlation coefficients will be used to estimate the connection between the seed region and all of the voxels within the whole brain separately based on the patients. Statistical significance will be set at *P*<.05 (2-sided).

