## Discussion

### Overview

This randomized controlled trial investigates the clinical efficacy and potential mechanism of Tuina in treating LDH. The results of this trial will be helpful in clarifying the cerebral mechanism of Tuina in the treatment of LDH. LDH occurs when the annulus fibrosus of the lumbar intervertebral disc tears, the nucleus pulposus herniates, and the dural sac and nerve root are stimulated and compressed [1]. This causes a wide range of symptoms, including low back pain, radiation pain in the lower limbs, and numbness. Pain, the primary symptom of LDH, is usually the main reason for patients to seek medical treatment [34].

Tuina is a traditional Chinese medicine treatment method based on meridian acupoint theory and modern anatomy [35]. A therapist manipulates the patient’s skin, muscles, and bones with both hands, including pressing, kneading, pushing, pulling, and shaking. Tuina is widely used for the treatment of LDH in China because of its proved effectiveness in relieving pain and muscle tension and improving dysfunction [35,36]. Traction is a technique used for stretching soft tissue and separating joint surfaces or bones to achieve the treatment goal [37]. Through electrodes placed on the skin, TENS creates pulsed alternating current. This can help relieve pain by activating the central nervous system’s endogenous inhibition mechanism [38-40]. The *Chinese Journal of Evidence-Based Medicine* published the “Evidence-based practice guide for nonoperative treatment of LDH” in 2024, listing Tuina, traction, and TENS as routine treatments and interventions for LDH [41].

Pain is considered to be an unpleasant and emotional feeling related to actual or potential histopathology [42]; therefore, changes in pain perception should include subjective and objective indicators. This study will use subjective SF-MPQ and ODI scores to assess changes in pain perception and dysfunction, while the objective index of tenderness threshold will demonstrate changes in pain symptoms. The combination of subjective and objective indicators can comprehensively reflect the changes in the symptoms of patients with LDH, reducing the occurrence of potential bias and improving the quality of clinical evidence.

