### Conclusions

This trial aims to investigate the cerebral mechanism of Tuina in the treatment of LDH. We used TENS combined with traction as a control intervention. We expect that Tuina can relieve pain symptoms in patients with LDH and that this pain relief mechanism is related to the activation or inhibition of pain-related regions in the brain.

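### The claim to show Tuina's cerebral mechanism goes beyond what an unblinded comparison of two active treatments can support

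*Protocol article*

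**What the plan says.** The Trial Design section sets up two arms: "the Tuina intervention group and traction with transcutaneous electrical nerve stimulation (TENS) intervention group". The closing Conclusions confirm the comparator's role: "We used TENS combined with traction as a control intervention". No sham or untreated arm is described. Under Blinding, patients and therapists know the allocation; only outcome evaluators and statisticians are blinded.

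The abstract's Objective is comparative: Tuina against TENS with traction. The claims made for the trial go further. The abstract's Conclusions say it "will show the cerebral mechanism of Tuina in LDH treatment by using fMRI". The closing Conclusions state: "We expect that Tuina can relieve pain symptoms in patients with LDH and that this pain relief mechanism is related to the activation or inhibition" (the sentence goes on to name brain areas linked to pain). The Discussion (Overview and the text after it) also frames the study as one of Tuina's own efficacy and mechanism.

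On the comparator, the Overview says of TENS: "This can help relieve pain by activating the central nervous system’s endogenous inhibition mechanism".

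Under Statistical Analysis, SF-MPQ, PPT and ODI are compared between groups by the Mann-Whitney U test, and "the Wilcoxon symbolic test will be applied for the intragroup comparison". For ALFF and ReHo a paired t test is named, described as a comparison of the two groups. Study Limitations mentions only that participants and operators cannot be blinded.

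**The concern.** The stated conclusion concerns Tuina itself: how it acts in the brain and that this explains its pain relief. Two quantities are available to support it, and neither isolates Tuina's effect.

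The first is pre-post change in the Tuina arm. Patients enter under the criterion "patients who did not take painkillers or nutritional neurodrugs for nearly 1 month and did not receive systematic treatment", with a neuropathic pain score of at least 4 and no criterion on symptom duration. Some change over 14 days without any specific treatment effect is therefore plausible: natural course, regression to the mean after selection on a score, expectation in patients who know their treatment, and effects of being scanned a second time.

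The second is the contrast between arms. It is a contrast with a treatment that, by the protocol's own account, has at least one centrally acting component. Effects common to both treatments cancel, and a difference may come from either arm.

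At stake is the headline conclusion. Pre-post change could be credited to Tuina, or a null contrast read as absence of a mechanism, and the design supports neither reading.

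**Working it through.** The claim itself rests on no figure in the article, so the main check is what each planned comparison estimates. Power figures follow, to show how the two kinds of test would behave.

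**What is estimated.** Assume additive effects on a brain or pain measure. Let
- N = natural course, regression to the mean and repeat-scan change, equal in expectation across arms because of randomisation;
- E_T and E_C = expectation effects in the Tuina and control arms, which may differ because patients are unblinded;
- T = the specific effect of Tuina; C = that of TENS with traction.

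Then
- change within the Tuina arm = N + E_T + T;
- change within the control arm = N + E_C + C;
- between-arm contrast of change = (T − C) + (E_T − E_C).

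The within-arm change equals T only if N + E_T = 0, which nothing in the design secures. The contrast equals T only if C = 0 and E_T = E_C. C = 0 does not fit the Overview's account of TENS, and E_T = E_C cannot be assumed without blinding.

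**Reading the contrast.** A null result fits T = C ≠ 0 (both act alike), T = C = 0 (neither acts), or T ≠ C with the difference missed. A non-null result shows a relative effect but does not say which arm produced it.

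**Which tests are planned.** The Wilcoxon tests are within-arm by definition. The paired t test for ALFF and ReHo is described as comparing the two groups, but patients in two independently randomised arms are not paired. The named test can validly be run only pre-post within an arm, and it would then estimate N + E_T + T.

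**Sample size used.** Sample Size Calculation gives 30 per group before dropout. The dropout step reproduces: 30/(1 − 0.20) = 37.5, rounded up to 38 per group, or 76 in all (that section prints 72; Trial Design has 76). The stated means and SDs give about 15 per group by a two-sided t test at power .85, not 30. These are separate matters; 30 is used here only as the number of completers per arm.

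**Between-arm precision.** Inputs are the post-treatment VAS SDs in the same section, 1.16 and 1.26:
- pooled SD = √[(1.16² + 1.26²)/2] = √1.4666 = 1.21;
- 95% CI half-width = t(0.975, 58) × 1.21 × √(2/30) = 2.00 × 1.21 × 0.258 ≈ 0.63 VAS points, or 0.52 SD;
- power, two-sided .05, one test without voxel correction: 21% for a difference of 0.3 SD, 48% for 0.5 SD.

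**Within-arm sensitivity.** Paired t test, 30 patients, two-sided .05: power 75% for a mean change of 0.5 SD of the change and 99% for 0.8 SD. This holds whatever mixture of N, E_T and T produced the change.

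**The case against.** The strongest reply is that the trial is already comparative. The abstract's Objective says so, and the sentence containing the disputed claim opens by promising a comparison of effectiveness. Pain relief is stated as an expectation, and other sections speak of exploring a potential mechanism. The comparator is defensible, since the Overview cites a practice guide listing all three treatments as routine. All of this stands: the design suits its stated objective, and the excess lies in what is concluded from it.

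It can also be said that no section announces that mechanism will be read from one arm's maps, or that a null contrast will be taken as no mechanism. That is correct, so a reader should not infer that the plan commits to either. The risk is nevertheless in the text, because within-arm significance tests are planned and the imaging test, as named, is valid only within an arm.

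Some stronger readings are not supported:
- That the between-arm contrast is free of non-specific effects. Randomisation balances natural course and repeat scanning in expectation, but not expectation effects among unblinded patients.
- That the whole control treatment acts centrally. The protocol says this of TENS, not of traction.
- That the trial is flawed for lacking healthy controls. Change toward healthy brain activity appears in the Introduction only as a prior study's result; this trial does not promise it.

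**Conclusion.** The concern holds as a mismatch between claim and design. The trial can estimate how Tuina and TENS with traction differ in their effect on brain measures and pain, subject to possible differential expectation. It cannot show Tuina's own cerebral mechanism, and a null contrast would settle nothing about one.

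The documents do not say how much central effect the two treatments share, so the loss in the contrast cannot be quantified. The conclusion does not depend on that. It needs only that N + E_T is not known to be zero and that C is not known to be zero. The power figures assume 30 completers per arm and approximate normality; the VAS half-width also assumes that the quoted post-treatment SDs apply. The between-arm figures are for a single test, and voxel-level correction would lower that power.

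The comparison survives and the choice of an active comparator is not in question. The headline conclusion should be changed.

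**What to change.** 1. In the abstract's Conclusions, the Discussion (Overview and the paragraphs after it) and the closing Conclusions, word the aim and expected finding as the between-arm difference in change in ALFF, ReHo, FC and pain, in line with the abstract's Objective.
2. Under Statistical Analysis, base inference on the between-arm contrast of change for both imaging and clinical outcomes, and describe the ALFF/ReHo test accordingly.
3. Report within-arm changes as descriptive estimates with intervals, without significance tests and without attributing them to Tuina.
4. State in advance that regions changing alike in both arms are evidence neither for nor against a Tuina mechanism.
5. Add to Study Limitations that the only comparator is active and that unblinded expectation may differ between arms.

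No new arm, scan or patient is needed. The article reports that data were still being collected and no analysis had been done, so the change could precede any results. The cost is a narrower claim.

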**Trial Registration:**

Chinese Clinical Trial Registry ChiCTR2400083784; https://www.chictr.org.cn/showproj.html?proj=225157

**International Registered Report Identifier (IRRID):**

DERR1-10.2196/63852

## Introduction

Lumbar disc herniation (LDH) is a common clinical disease, which is caused by the rupture of the annulus fibrosus of the lumbar intervertebral disc, herniation of nucleus pulposus, and stimulation and compression of the dural sac and nerve root, leading to a series of symptoms such as low back pain, lower limb radiation pain, and numbness [1]. LDH is more prevalent among individuals aged 30-50 years, and the lifetime risk for symptomatic LDH is 1%-3%. In contemporary society, due to poor lifestyles and lack of exercise, the incidence of LDH is increasing every year and is frequently reported among younger male populations; therefore, LDH has become a serious public health and socioeconomic problem [2].

The pathogenesis of pain caused by LDH is complex, mainly involving the central and peripheral nervous systems. The peripheral mechanism is usually attributed to mechanical compression or local inflammation of the nerve roots caused by LDH [3]. For example, larger protrusions lead to lumbar spinal nerve root damage and induce changes in nerve fibers, and inflammatory response–related factors result in local inflammation in the microenvironment, leading to LDH pain. At the same time, related inflammatory mediators in LDH, such as interleukin-1β, interleukin-6, interleukin-8, tumor necrosis factor-α, and interferon γ, can also synchronously stimulate peripheral nerve endings and receptors and lead to LDH pain [4,5]. However, the peripheral mechanism alone is not enough to explain the complex clinical symptoms caused by LDH, such as pain sensitization, anxiety, and depression, which are often observed in patients with LDH [6,7]. Therefore, the central mechanism is considered to play a key role in the etiology of LDH.

Functional magnetic resonance imaging (fMRI) is an imaging technique that depicts the neural activity in the brain in real time based on the changes in local oxygen consumption and cerebral blood flow [8]. fMRI is widely used in pain-related research, and it can detect the effects of different types of pain on brain activity. A number of studies have shown that structural and functional changes can occur in the brains of patients with LDH [9]. Among them, a prospective study found that the volume of gray matter volume in the right anterolateral prefrontal cortex, right temporal lobe, left premotor cortex, right caudate nucleus, and the right cerebellum decreased significantly, while the volume of the right dorsal anterior cingulate cortex, left precuneal cortex, left fusiform gyrus, and the right brainstem increased in patients with LDH, suggesting that LDH can cause specific local changes in the brain structure [10]. In patients with LDH, the amplitude of low-frequency fluctuations (ALFF) increased in the right lingual gyri in the conventional band and in the left Cerebelum_Crus1 in the slow-4 band [11]. In addition, patients with LDH also have impaired excitability of the somatosensory and motor cortex, decreased homogeneity of the default mode network, and dysfunction of functional connectivity (FC) [12]. These findings suggest that brain structural remodeling and functional changes may be the cerebral mechanism of the pathogenesis of LDH.

At present, the treatment of LDH mainly includes conservative treatment, interventional therapy, and surgical treatment [13]. Tuina is a massage therapy guided by traditional Chinese medicine theory, which has a long history. Recently, several randomized controlled trials have confirmed the positive effects of Tuina treatment [14-16]. For example, Tuina has a good therapeutic effect on diseases such as LDH, chronic neck pain, and knee osteoarthritis. A meta-analysis of 13,075 patients also showed that Tuina is more effective than traction and Chinese herbal medicine in the treatment of LDH [17]. However, the mechanism of Tuina in the treatment of pain in LDH has not been fully elucidated, and the potential cerebral mechanism of Tuina analgesia is a hot topic of interest.

Recently, some scholars have used fMRI technology to study the central mechanism of Tuina in the treatment of LDH pain and obtained some positive results. For example, Zhou et al [18] found that patients with LDH showed abnormal brain ALFF and regional homogeneity (ReHo) values, which were altered after Tuina manipulation. Patients with LDH showed decreased ReHo in the left orbital part of the middle frontal gyrus, decreased dynamic FC (dFC) variance between the left orbital part of the middle frontal gyrus and the left fusiform, and increased dFC variance in the left orbital inferior frontal gyrus and left precuneus. Tuina therapy positively altered the ReHo and dFC values, making the brain activities in patients with LDH similar to those in healthy controls [12].

In recent years, although many studies [12,19] have provided evidence on the central brain mechanism of Tuina analgesia by using fMRI technology, relatively few studies have explored the central mechanism of Tuina in the treatment of LDH. Therefore, we designed a randomized controlled trial to explore the potential cerebral mechanism of Tuina analgesia by using fMRI.

## Methods

### Trial Design

This is a single-center randomized controlled trial with 2 parallel arms: the Tuina intervention group and traction with transcutaneous electrical nerve stimulation (TENS) intervention group. A total of 76 eligible patients with LDH will be recruited for this trial, and patients with LDH will be randomly assigned to the groups in 1:1 ratio. All patients will provide written informed consent. Outcome evaluation and statistical analysis will be performed by 2 researchers who do not know the specific groups. The trial design flowchart is shown in Figure 1, and the study schedule is shown in Figure 2. This study will be conducted in the Rehabilitation Hospital affiliated to Fujian University of Traditional Chinese Medicine. This study follows the CONSORT (Consolidated Standards of Reporting Trials) guidelines (Multimedia Appendix 1).

**Figure 1 figure1:**
[figure not shown]
Flowchart of this trial. fMRI: functional magnetic resonance imaging; ODI: Oswestry disability index; PPT: pressure pain threshold; SF-MPQ: Short-Form McGill Pain Questionnaire; TENS: transcutaneous electrical nerve stimulation.

**Figure 2 figure2:**
[figure not shown]
Flow diagram of this study. –3 to 0 days: within 3 days prior to treatment; 0 day: day 0 of treatment; 1 day: day 1 of treatment; 7 days: day 7 of treatment; 10 days: day 10 of treatment; 14 days: day 14 of treatment; 1 month: 1 month after treatment; fMRI: functional magnetic resonance imaging; ODI: Oswestry disability index; PPT: pressure pain threshold; SF-MPQ: Short-Form McGill Pain Questionnaire; TENS: transcutaneous electrical nerve stimulation.

### Ethics Approval

The study protocol has been approved by the ethics review committee of The Rehabilitation Hospital affiliated to Fujian University of Traditional Chinese Medicine (project 2024KY-008-02). This study was registered on May 1, 2024, with the Chinese Clinical Trial Registry (ChiCTR2400083784).

